## Abstract

**Introduction:**

The aim of this large, prospective, double-blind randomized controlled trial is to investigate the effect of atorvastatin on the formation of collateral blood vessels in patients after encephaloduroarteriosynangiosis (EDAS) and to provide a theoretical basis for clinical drug intervention. Specifically, we will determine whether atorvastatin has an effect on the development of collateral vascularization and on cerebral blood perfusion after revasculoplasty in patients with moyamoya disease (MMD).

**Methods and analysis:**

Overall, 180 patients with moyamoya disease will be recruited and randomly assigned to the atorvastatin treatment group or the placebo control group in a 1:1 ratio. Before revascularization surgery, magnetic resonance imaging (MRI) scanning and digital subangiography (DSA) examination will be routinely performed on the enrolled patients. All patients will receive intervention via EDAS. According to the randomization results, patients in the experimental group will be treated with atorvastatin (20 mg/day, once a day, for 8 weeks) and patients in the control group will be treated with placebo (20 mg/day, once a day, for 8 weeks). All participants will return to the hospital for MRI scan and DSA examination 6 months after EDAS surgery. The primary outcome of this trial will be the difference in the formation of collateral blood vessels revealed by DSA examination at 6 months after EDAS surgery between the two groups. The secondary outcome will be an improvement in the dynamic susceptibility contrast sequence cerebral perfusion on MRI at 6 months after EDAS, compared to the preoperative baseline.

**Ethics and dissemination:**

This study was approved by the Ethics Committee of the First Medical Center of the PLA General Hospital. All participates will voluntary provide written informed consent before participating in the trial.

**Clinical trial registration:**

ClinicalTrials.gov, ChiCTR2200064976.

## Introduction

1.

Moyamoya disease (MMD) is a rare, chronic, and progressive cerebrovascular disorder characterized by stenosis and occlusion of the distal carotid, proximal middle, and anterior cerebral arteries and is accompanied by the development of small collateral vessel networks (1, 2). If the newly-formed collateral vessels do not maintain sufficient cerebral perfusion, it can lead to ischemic events, particularly in pediatric patients who require more blood flow for cerebral development and maturation.

At present, there is no effective drug for treating MMD, and revascularization surgery for symptomatic MMD is considered the standard treatment for preventing further strokes. Cerebrovascular reconstruction can form new collateral networks, improve cerebral blood flow reserve, and reduce the occurrence of secondary strokes, and has become the preferred approach of many neurosurgeons (3). Encephaloduroarteriosynangiosis (EDAS) is one of the most used indirect revascularization procedures and is a widely established treatment strategy for patients with MMD due to its excellent postoperative results, leading to extensive collateral vessels formation and minimal complications. However, in our previous long-term follow-up studies, we found that approximately 20% of patients had poor postoperative collateral circulation (4, 5). A recent study performed by our center showed that the formation of collateral vessels in EDAS is primarily driven by angiogenesis, and the endothelial progenitor cell (EPC) count may be the most critical factor for promoting the development of collateral networks (6). An increase in the proliferation and activation of EPCs may lead to better collateral circulation in patients.

Atorvastatin, a classic lipid-lowering drug, has been widely used in the cardiovascular field. Earlier literature indicated that statins can affect the mobilization, proliferation, chemotaxis, and apoptosis of EPCs (7, 8). Our previous retrospective study found that the extent of postoperative formation of collateral vessels in patients with atorvastatin treatment was significantly higher than in the control group (9). This provides a novel option in the treatment of MMD, which may ensure a better outcome in patients receiving EDAS surgery. However, the benefit remains to be confirmed by a large prospective randomized controlled study.

Therefore, we plan to explore whether atorvastatin can promote the formation of collateral vessels after EDAS and provide evidence for its beneficial use as adjuvant treatment in MMD.

## Methods and analysis

2.

### Study design

2.1.

This will be a single-center, prospective, randomized, double-blind, placebo-controlled study (Figure 1). A total of 180 patients will be recruited from the Department of Neurosurgery, Chinese PLA General Hospital, and randomly assigned to the atorvastatin treatment or the placebo control group at a ratio of 1:1. The study is planned to run from October 2022 through October 2025.

**Figure 1 fig1:**
[figure not shown]
Study flow chart. MMD, moyamoya disease; EDAS, encephaloduroarteriosynangiosis.

### Inclusion and exclusion criteria

2.2.

Participants will be recruited from the hospital wards. Inclusion criteria are as follows: (a) patients are diagnosed with MMD according to the 2021 Japanese Guidelines for the “Management of Moyamoya Disease: Guidelines from the Research Committee on Moyamoya Disease and Japan Stroke Society,” where DSA or magnetic resonance angiography shows stenosis or occlusion at the distal end of the internal carotid artery or anterior cerebral artery and/or middle cerebral artery, and abnormal proliferation and smoky vascular network can be found near occluded or stenosis vessels in the arterial phase of angiography (10); (b) patients are at a stable stage of the stroke, without acute or subacute cerebral infarction or cerebral hemorrhage, and more than 3 months after the last cerebral infarction or cerebral hemorrhage; (c) age ≥ 18 years; (d) no previous intracranial and extracranial vascular reconstruction; (e) complete understanding of the nature and content of the study, voluntary participation, and provision of written informed consent.

Exclusion criteria are as follows: (a) long-term statin therapy; (b) long-term steroid therapy; (c) acute or subacute cerebral infarction or cerebral hemorrhage; (d) allergy to statins or their ingredients; (e) abnormal renal and liver function; (f) uncontrolled hepatitis and other liver diseases, as well as other diseases that may interfere with the study; (g) pregnancy or lactation; (h) meningitis, autoimmune diseases, multiple neurofibromatosis, down syndrome, craniocerebral trauma, intracranial tumors, radiation damage, and other underlying diseases that may cause smog; (i) participation in a different experimental treatment study at the same time; and (j) failure to successfully complete the test due to poor compliance.

### Randomization and treatment allocation

2.3.

All enrolled patients will be randomly assigned to the atorvastatin treatment group or the placebo control group in a 1:1 ratio (*n* = 90 for each). The randomization sequence will be obtained according to the SPSS software program, and the randomization process will not be stratified. The randomized sequences of group assignments are then hidden in sequentially numbered opaque, closed envelopes. Atorvastatin (Pfizer) and placebo will be stored at the participating hospitals (20–30°C, while avoiding direct lighting), and they will be handled exclusively by the study nurses responsible for drug storage, distribution, and documentation. Placebo tablets are made from dextrin and have the same weight and appearance as atorvastatin. Two types of tablets are made by Shandong ARURA Pharmaceutical Research and Development Co., based on a randomized sequence, and are numbered sequentially. The randomization information and drug type are not publicly available to all investigators, competent physicians, and patients. All patients will be numbered sequentially, and the 8-week dose will be dispensed by the medication nurse in numbered order. At the end of the follow-up visit for the last enrolled patient, the sealed, opaque envelope will be opened by the principal investigator with unblinding (11).

### Intervention

2.4.

Patients in both groups will undergo standard EDAS procedures. EDAS surgery will be performed by experienced neurosurgeons. The main steps are as follows: (i) in accordance with the blood supply artery, contour the scalp with an incision design, (ii) cut the skin and subcutaneous free out long enough blood supply arteries, (iii) drill a hole on both ends of the bone flap, (iv) form an ellipse milling cutter governor of bone flap, (v) cut an open bar and epidural of about 1-cm width, (vi) maintain epidural blood vessels as far as possible, (vii) sew with fascia artery blood supply on cut epidural, and (viii) return the flap and fix it. The supplying artery remains open.

According to the results of randomization, patients in the experimental group will receive atorvastatin (20 mg/day, once a day, for 8 weeks), and patients in the control group will receive placebo (20 mg/day, once a day, for 8 weeks) from the first day after surgery (11). This dosage was chosen because it had minimal side effects in hyperlipidemia (12, 13), and because a high dose of atorvastatin (80 mg) was shown to increase the risk of bleeding in patients with low body weight and uncontrolled hypertension in a stroke prevention trial that focused on aggressively lowering cholesterol levels (14). Liver and kidney function tests will be performed every 4 weeks during treatment. All drug-related adverse reactions will be communicated to the investigators in a timely manner, and the investigators will decide whether to conduct clinical intervention or withdraw from the study according to the patient-specific situation. All drug-related adverse effects will be documented in detail.

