#### Safety outcomes assessment

2.5.1.

We will evaluate the safety of atorvastatin calcium tablets based on the following events: (1) presence of abnormal liver and kidney function; (2) severe adverse drug reactions, such as death, life-threatening or permanent or severe disability, permanent organ dysfunction, emergency hospitalization or prolonged hospitalization; and (3) new strokes occurring during follow-up after EDAS.

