#### The secondary outcomes

2.5.3.

Dynamic Susceptibility Contrast-Magnetic Resonance Imaging examination will be performed to evaluate the improvement of cerebral hemodynamic parameters at 6 months after EDAS, compared to the preoperative baseline level. The time to peak contrast will be used to assess the patient’s hemodynamic status, with mean transit time and hemodynamic parameters calculated by perfusion (16).

The modified Rankin Scale (mRS) score will be used to evaluate the improvement of clinical symptoms of the patients before surgery and at 6 months after surgery. The mRS scores will be used to evaluate the degree of disability or dependence in daily activities of the patients, and the improvement of mRS score in the two groups will be compared and analyzed before surgery and 6 months after surgery (17).

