### Sample size estimation

3.2.

Using the normal approximation method and Pearson Chi-square test sample size calculation formula for the rate comparison between the two groups, test level *α* = 0.05 and test efficiency 1−β = 0.80 were set. According to the preliminary experimental results of this project, the probability of formation postoperative collateral networks (grade A or grade B) in patients with MMD treated with atorvastatin was 79.1%. The incidence in development of postoperative collateral vessels (grade A or B) in patients with MMD who were not treated with atorvastatin was 58.2%. Assuming that the coefficient of sample size relationship between the experimental group and the control group, K, is equal to 1, the minimum sample size for the two groups was calculated as *n* = 77, with the estimated loss to follow-up rate and rejection rate at 10%. The final total minimum sample was *n* = 154/0.9 = 172. We ultimately began with 180 cases.

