### Statistical analysis

3.3.

All data will be analyzed by intention-to-treat and per-protocol. Categorical variables will be analyzed by chi-square test and continuous variables will be compared by independent *t*-tests or ANOVA. A U-test will be performed for variables that do not follow a normal distribution. Univariate analysis will be used to assess age, sex, initial symptoms at diagnosis, collateral grade, posterior circulation involvement, and use of atorvastatin. Variables significantly associated will be selected and analyzed by multiple linear regression. A value of *p* < 0.05 will be considered statistically significant. SPSS 26.0 software will be used for statistical analysis of all data.

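### Section 2.4 answers a drug reaction with withdrawal from the study instead of stopping the tablets, which puts the 6-month outcomes of those patients at risk

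*Protocol article*

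**What the plan says.** Section 2.4 (Intervention) of the protocol article gives 8 weeks of tablets from the first day after surgery. On monitoring it says "Liver and kidney function tests will be performed every 4 weeks during treatment". For a drug-related adverse reaction it says "the investigators will decide whether to conduct clinical intervention or withdraw from the study according to the patient-specific situation". The first option, clinical intervention, is not defined. Stopping tablets while staying in follow-up is not mentioned.

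Other sections depend on complete follow-up:

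- Abstract, Methods and analysis: "All participants will return to the hospital for MRI scan and DSA examination 6 months after EDAS surgery".
- Section 2.5.1 (Safety outcomes assessment) counts "new strokes occurring during follow-up after EDAS".
- Section 2.5.2 (The primary outcomes) reads collateral formation by DSA at 6 months.
- Section 2.5.3 (The secondary outcomes) sets MRI perfusion at 6 months against the preoperative baseline and states that "the improvement of mRS score in the two groups will be compared and analyzed before surgery and 6 months after surgery".
- Section 3.3 (Statistical analysis): "All data will be analyzed by intention-to-treat and per-protocol".

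**The concern.** Stopping a drug and leaving a trial are different events. An intention-to-treat comparison needs the outcome of every randomised patient, whether or not the tablets were taken to the end. In its ordinary sense, the wording of section 2.4 lets an investigator end a patient's participation because of a reaction, months before the primary outcome is read.

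The trigger matters. It is a reaction to study drug, and the comparator is a dextrin placebo, so these losses are plausibly more frequent on atorvastatin. Outcomes would then be missing for a reason linked to treatment, and the randomised comparison of 6-month collateral grade would lose some of its protection. The safety comparison is exposed too: a stroke after withdrawal may go unrecorded in just those patients whose tolerance of the drug was in doubt. An analysis plan cannot repair this later, because a DSA not done at 6 months cannot be recovered.

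**Working it through.** **Inputs from the protocol article.** Good grade (A or B) 79.1% with atorvastatin and 58.2% without; α = 0.05; power 0.80; 10% allowed for loss to follow-up and rejection (section 3.2). 90 patients per arm (section 2.3). Tablets for 8 weeks, laboratory tests every 4 weeks (section 2.4). Outcome at 6 months (section 2.5), taken here as 26 weeks.

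**Assumptions.** The article gives no reaction rate, no withdrawal rate and no outcome rate for withdrawn patients. I let w, the fraction withdrawn on atorvastatin only, be 5% or 10% (4.5 or 9 of 90). I let g, the good-grade rate those patients would have had, run from 29.1% (half of 58.2%) to 40%.

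**1. The plan's own sample size.** Two-sided test, pooled normal approximation, no continuity correction. The mean rate is (0.791 + 0.582)/2 = 0.6865.

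n = {[1.96·√(2·0.6865·0.3135) + 0.8416·√(0.791·0.209 + 0.582·0.418)] / 0.209}² = 76.2, rounded up to 77 per arm.

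Then 154/0.9 = 171.1, rounded up to 172. Both figures match section 3.2.

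**2. Time that could go unobserved.**
- Withdrawn at the week-4 test: 26 − 4 = 22 of 26 weeks.
- Withdrawn at week 8: 26 − 8 = 18 of 26 weeks.

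**3. Bias when the drug has no effect.** Set both arms to 58.2%. The rate among atorvastatin patients who stay is (0.582 − w·g)/(1 − w), and the bias is that rate minus 0.582.

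| w | g | Observed rate | Bias (points) |
|---|---|---|---|
| 5% | 40% | 59.2% | +1.0 |
| 5% | 29.1% | 59.7% | +1.5 |
| 10% | 40% | 60.2% | +2.0 |
| 10% | 29.1% | 61.4% | +3.2 |
| any | 58.2% | 58.2% | 0 |

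The extreme g = 0 gives +3.1 points at w = 5% and +6.5 at w = 10%. If withdrawn patients would have done better than the rest (g above 58.2%), the sign reverses.

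**4. Power under loss.** At the planned rates, power is 86.2% with 90 per arm and 82.4% with 81 per arm (10% lost in each). Losing a further 2%, 5% or 10% of the 90 in the atorvastatin arm leaves 79.2, 76.5 or 72 there against 81 on placebo, and power of 81.9%, 81.2% or 79.9%. Loss of numbers is therefore not the main harm. The 10% allowance protects power, but enrolling more patients does not correct selective loss.

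**5. What keeping these patients does to the estimate.** Suppose those who stop early revert to 58.2%. The atorvastatin rate is then (1 − w)·0.791 + w·0.582.

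| w | Atorvastatin rate | Difference (points) | Power, 90 per arm | Power, 81 per arm |
|---|---|---|---|---|
| 0 | 79.1% | 20.9 | 86.2% | 82.4% |
| 5% | 78.1% | 19.9 | 82.1% | 77.9% |
| 10% | 77.0% | 18.8 | 77.4% | 72.9% |

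**The case against.** The best defence is that this is one loosely worded clause in a condensed article. It does not say whether the patient or the tablets are withdrawn. Clinical intervention is undefined and could include stopping tablets. The abstract says that all participants return at 6 months, strokes are counted after EDAS and not only during treatment, and a per-protocol set beside intention-to-treat suggests that patients who depart from treatment stay in the intention-to-treat data. Discontinuation rules often sit in the full protocol, which is not shown.

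The size is also assumed. Investigators are blinded, patients with abnormal liver or kidney function or statin allergy are excluded, and the dose has a safety rationale: "This dosage was chosen because it had minimal side effects in hyperlipidemia". Nothing in the article links a tablet reaction to poorer collateral growth. At 1-2% withdrawn, the same formula gives only 0.2 to 0.6 points. Even 3.2 points is less than half the standard error of the difference, √(2·0.582·0.418/81) = 7.8 points.

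The points about size stand, and they keep this a modest issue. Those about reading do not remove it. However clinical intervention is understood, the other branch still permits ending participation for a reaction. If the abstract's statement is meant to cover these patients, then withdrawal from the study is the wrong phrase and needs the same correction. This is a rule that the article states, not a detail that it leaves out.

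**Conclusion.** The concern holds and should be fixed, with medium confidence. Followed as written, section 2.4 can cost patients who react to the tablets their 6-month DSA, MRI and mRS and their stroke follow-up, at odds with the abstract and the intention-to-treat analysis. No sentence says that follow-up stops for them, and withdrawal is discretionary, so the loss is possible, not certain.

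The likely harm is bias, probably small: 1.0 to 3.2 points in favour of atorvastatin under the assumed 5-10% withdrawal on that arm alone and a 29-40% good-grade rate in those withdrawn. It is less with fewer withdrawals and nil if the withdrawn patients resemble the others. The stated sample size is correct and needs no change on this account.

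**What to change.** In section 2.4, replace withdrawal from the study with discontinuation of study tablets as the investigator's option after a reaction. Add that patients who stop tablets keep the scheduled 6-month DSA, MRI and mRS and the stroke follow-up, and are analysed in their assigned arm. Reserve withdrawal from the study for withdrawn consent. When and in whom tablets are stopped remains the investigator's decision, so safety discretion is untouched.

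The cost is one or two sentences by amendment. No procedure is added, because these assessments are already planned for all participants. The downside is the dilution in step 5: at 5-10% early stopping, power falls to 82-77% with 90 per arm, or to about 78-73% if a further 10% of each arm is lost for other reasons. That smaller difference is the effect of assignment, which is what intention-to-treat is meant to estimate.

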### Outcomes

2.5.

#### Safety outcomes assessment

2.5.1.

We will evaluate the safety of atorvastatin calcium tablets based on the following events: (1) presence of abnormal liver and kidney function; (2) severe adverse drug reactions, such as death, life-threatening or permanent or severe disability, permanent organ dysfunction, emergency hospitalization or prolonged hospitalization; and (3) new strokes occurring during follow-up after EDAS.

#### The primary outcomes

2.5.2.

The main outcome will be the formation of collateral blood vessels in patients 6 months after EDAS and it will be measured by DSA. Additionally, we will compare whether there are statistical differences between the experimental and the control group and analyze whether there is a correlation between the effect of vascular reconstruction and the application of atorvastatin.

The standard evaluation of the formation of collateral vessels relies on the Matsushima grading: grade A, the superficial temporal artery compensates to the intracranial mass, covering more than 2/3 of the blood supply area of the middle cerebral artery; grade B, the superficial temporal artery compensates to the intracranial middle one in equal amount, covering 1/3–2/3 of the blood supply area of the middle cerebral artery; grade C, there is no communication between the superficial temporal artery and the intracranial one, no growth to the intracranial artery, or a small amount of compensation from the superficial temporal artery to the intracranial one, covering 0–1/3 of the blood supply area of the middle cerebral artery (15).

#### The secondary outcomes

2.5.3.

Dynamic Susceptibility Contrast-Magnetic Resonance Imaging examination will be performed to evaluate the improvement of cerebral hemodynamic parameters at 6 months after EDAS, compared to the preoperative baseline level. The time to peak contrast will be used to assess the patient’s hemodynamic status, with mean transit time and hemodynamic parameters calculated by perfusion (16).

The modified Rankin Scale (mRS) score will be used to evaluate the improvement of clinical symptoms of the patients before surgery and at 6 months after surgery. The mRS scores will be used to evaluate the degree of disability or dependence in daily activities of the patients, and the improvement of mRS score in the two groups will be compared and analyzed before surgery and 6 months after surgery (17).

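### Secondary outcomes are worded as improvement from baseline, perfusion without a named arm comparison, with unadjusted tests only; adjusting for the preoperative value would gain precision at no cost

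*Protocol article*

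**What the plan says.** **Perfusion.** Section 2.5.3 of the protocol article uses perfusion MRI to "evaluate the improvement of cerebral hemodynamic parameters at 6 months after EDAS, compared to the preoperative baseline level". The abstract describes the outcome in the same way. Neither place mentions the two arms, although the abstract's sentence on the primary outcome does.

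**mRS.** The next paragraph of section 2.5.3 does mention them: "the improvement of mRS score in the two groups will be compared and analyzed before surgery and 6 months after surgery".

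**Tests.** Section 3.3 says that "continuous variables will be compared by independent" t-tests or ANOVA, with a U-test for variables that are not normally distributed and chi-square for categorical ones. None of these uses the preoperative value as a covariate. The one multivariable step is a linear regression on variables kept because they were significant one at a time. Its candidates are age, sex, initial symptoms, collateral grade, posterior circulation involvement and atorvastatin use. Preoperative perfusion and preoperative mRS are not among them, and the dependent variable is not named.

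**Aim and design.** The abstract gives as an aim whether atorvastatin affects cerebral perfusion. Every patient has EDAS, and section 2.3 states that "the randomization process will not be stratified".

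**The concern.** Two things are fixed less well than they could be.

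First, the perfusion outcome as defined does not match the aim. Since both arms have surgery, improvement from baseline contains the effect of EDAS. Only a contrast between arms can isolate atorvastatin, and the definition leaves that contrast to be inferred.

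Second, both outcomes have a value measured before surgery and hence before study treatment, which starts on the first day after surgery. The named tests do not use it as a covariate. If improvement means a difference score, the comparison carries the full noise of the baseline measurement. It also responds to any chance baseline difference between arms: with equal standard deviations (SDs), a baseline difference of d shifts the change-score contrast by −(1 − r)d. For mRS, a difference score also has a floor, because a patient at 0 before surgery cannot improve.

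At stake is the power of the secondary comparisons and the clarity of what a perfusion result would mean.

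**Working it through.** **1. The plan's own figure.** Section 3.2 gives "test level *α* = 0.05", "test efficiency 1−β = 0.80 were set", and rates of grade A or B of 79.1% and 58.2%. Two-sided testing is assumed, because sidedness is not stated and one-sided testing would give 60.

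- Mean rate: (0.791 + 0.582)/2 = 0.6865; difference 0.209.
- n per arm = [1.960·√(2·0.6865·0.3135) + 0.8416·√(0.791·0.209 + 0.582·0.418)]² / 0.209² = 76.2, so 77.
- Total: 154/0.9 = 171.1, so 172, with 180 started.

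The stated size reproduces. It concerns the primary outcome only; none is given for perfusion or mRS. After 10% loss, 180·0.9/2 = 81 patients per arm are evaluable.

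**2. Precision for a continuous perfusion measure.** Let r be the correlation between the preoperative and 6-month values. The article does not give it, so 0.3 to 0.8 is assumed. With equal SDs at both times, and variance expressed relative to a comparison of 6-month values alone:

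- change score: 2(1 − r)
- ANCOVA: 1 − r²
- ratio of ANCOVA to change score: (1 + r)/2

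The detectable difference in SD units at 80% power is (1.960 + 0.8416)·√(2v/81), where v is the relative variance. For an effect that the change-score test detects with 80% power, ANCOVA has power Φ(2.8016/√ratio − 1.960).

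| r | v, change | v, ANCOVA | Ratio | Detectable, change | Detectable, ANCOVA | Power, ANCOVA |
|---|---|---|---|---|---|---|
| 0.3 | 1.40 | 0.91 | 0.65 | 0.52 | 0.42 | 93.5% |
| 0.5 | 1.00 | 0.75 | 0.75 | 0.44 | 0.38 | 89.9% |
| 0.7 | 0.60 | 0.51 | 0.85 | 0.34 | 0.31 | 86.0% |
| 0.8 | 0.40 | 0.36 | 0.90 | 0.28 | 0.26 | 84.0% |

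At r = 0.5 a change-score analysis needs 1/0.75 = 1.33 times as many patients for the same precision.

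**3. If the SDs differ.** Let the preoperative SD be k times the 6-month SD. The change-score variance is then 1 + k² − 2rk. Subtracting 1 − r² leaves (k − r)², which is never negative. So apart from the negligible cost of estimating one slope, ANCOVA is at least as precise for any k, but the size of the gain moves. At r = 0.5, k = 0.8 gives 0.75/0.84 = 0.89 and k = 1.25 gives 0.75/1.3125 = 0.57, against 0.75 at k = 1.

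**4. If improvement was not meant as a difference.** Against a plain comparison of 6-month values the ratio is 1 − r²: 0.91, 0.75, 0.51 and 0.36 at the four correlations. The advice does not depend on which unadjusted version was intended.

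**5. mRS.** These formulas are for continuous outcomes. mRS is ordinal, so none of the figures above carries over to it.

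**The case against.** A reader might infer that perfusion will be tested only before against after within each arm, which could not show a drug effect. The documents do not support that. The abstract states the aim as an effect of atorvastatin, section 3.3 names independent two-sample tests, and no paired or within-arm test appears anywhere. What stands is that the definition omits an arm comparison which the rest of the article implies.

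A reader might also infer that the planned comparisons are biased. They are not. An unadjusted comparison of change between randomised arms is unbiased over randomisation. Regression to the mean matters only given a chance imbalance, and with 90 per arm the standard error of a baseline difference is √(2/90) = 0.15 SD. Lack of stratification does not in itself make imbalance in perfusion or mRS more likely than stratifying on other factors would. What remains is lower precision and some sensitivity to chance imbalance.

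Three further points are fair. The article never says outright that the tested variable is a difference; that is inferred from the word improvement, and an improved or not-improved category under chi-square is also possible. The gain rests on an assumed r and is small when r is high. For mRS, a rank test between randomised arms is valid, and a proportional-odds model brings an assumption of its own.

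Finally, a condensed article may leave model detail to a fuller document. That would answer silence. Here the article does choose the form of the outcome, the tests and the list of covariates, and the preoperative values are missing from that list.

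**Conclusion.** The point holds as one of definition and precision in secondary outcomes. The perfusion outcome should name its between-arm comparison, and the named tests leave the preoperative values unused as covariates.

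For the continuous perfusion measures, ANCOVA would cut variance relative to change scores by 35% at r = 0.3, 25% at 0.5, 15% at 0.7 and 10% at 0.8. This rests on equal SDs at both times, an r that the article does not report, and the reading of improvement as a difference score. The direction does not need equal SDs; the size does. No gain is quantified for mRS.

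Nothing here invalidates the planned comparisons or touches the primary outcome or its sample size. The change is worth making because it is free, not because the present plan gives wrong answers.

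**What to change.** In section 2.5.3, with a matching sentence in section 3.3, state before unblinding:

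- Time to peak and mean transit time at 6 months are compared between arms by ANCOVA with the preoperative value as covariate. The adjusted difference is reported with its 95% confidence interval.
- mRS at 6 months is compared between arms by an ordinal model, for example proportional odds, adjusted for preoperative mRS.
- Changes from baseline within each arm are descriptive only.
- The preoperative value enters by specification, whether or not it is significant in a univariate screen.

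The abstract's perfusion sentence should name the two arms as well. The cost is wording. Both preoperative measurements are already planned, SPSS 26.0 fits both models, and no extra patients, visits or scans are needed.
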